## Abstract

**Background:**

The optimal therapeutic approach for early‐stage NSCLC (I–II, and, in some specific cases, IIIa) is lung resective surgery with mediastinal lymphadenectomy. However, it should be remarked that lung resection surgery further negatively affects respiratory muscle function and health‐related quality of life (HRQoL). It is well known that exercise interventions may improve pulmonary function but the optimal approach has not been determined yet.

**Aims:**

The aim of the present study is to investigate the results obtained by administering a specific athletic/physical protocol to a cohort of patients who undergo lung surgery after NSCLC diagnosis.

**Materials and Methods:**

Among patients who underwent a surgical treatment of NSCLC and followed in our Institution, those with the highest scores of performance status, defined after multidisciplinary evaluation by Interdisciplinary Group for Thoracic Neoplasms (GINT) will be addressed to the Interdipartimental Centre in Motor and Sport Activities, Sport Medicine Centre, University of Pavia for a work protocol based on mesocycles of 3times/week for 6 months.

**Results:**

Respiratory function, cardiopulmonary exercise capacity, caloric expenditure expressed as metabolic equivalents (METs), and health‐related quality of life will be assessed at baseline, 3 months, and 6 months in a prospective single‐arm pilot cohort. Caloric consumption will be measured by metabolic equivalents (MET). A quality of life (QoL) questionnaire and a spirometry will be administered to patients at the same intervals.

**Discussion:**

The primary exploratory endpoint will be the change in CPET‐derived VO₂peak from baseline to 6 months; secondary endpoints will include changes in FEV₁, DLCO, MIP/MEP, METs, muscle power, and EORTC QLQ‐C30 scores. For each patient, written informed consent will be obtained before the enrollment.

**Conclusion:**

Our study is, to the best of our knowledge the first perspective clinical trial encompassing athletic programs for patients with surgical treatment of NSCLC. The study is designed to provide preliminary data on feasibility, safety, and functional outcomes of a structured post‐surgical athletic intervention in carefully selected patients with early‐stage NSCLC.

## Introduction

1

Lung cancer is the predominant cause of cancer cases and deaths and causes significant health challenges. Non‐small cell lung cancer (NSCLC) includes a variety of histologically different tumors. The gold standard therapeutic approach for early‐stage disease is surgery. In patients with an adequate respiratory reserve, lobectomy has been the gold standard; however, recent results of the CALGB and JCOG/WJOC non‐inferiority trials clearly showed the oncological efficacy of a sublobar resection in early‐stage disease. Pneumonectomy is restricted to selected patients in cases of locally advanced, central tumors with invasion of vascular and/or bronchial structures. Surgery for lung cancer patients significantly impacts their quality of life, disability level, and functional profile [as defined by The International Classification of Functioning, Disability and Health (ICF), developed by the World Health Organization (WHO) [1, 2, 3, 4]. Assessing these parameters can aid in better understanding the full impact of surgical intervention, enhancing patient–surgeon communication, improving patient counseling and expectation setting, and monitoring treatment and therapeutic progress. It is reported that multimodal prehabilitation for lung surgery is feasible within a timeframe of 3 weeks. Even though this study was not powered to confirm it, prehabilitation may improve preoperative functional capacity [5]. However, the vast majority of available data regards the effects of Rehabilitation Exercises after thoracic surgery for NSCLC. It has been reported that this approach is effective for managing long‐term persistent postoperative symptoms, such as cough [6]. Post‐surgical rehabilitation improves cardiopulmonary function, encompassing respiratory muscle strength, ventilatory equivalent, tidal volume, stroke volume index, and cardiac index at peak exercise [4]. Some data are still available about physical activity after surgery: for instance, it has been reported that age and surgical procedure affect the increase in post‐operative walking steps [7]. However, data regarding a full training athletic program after surgery are still controversial [8]. Rehabilitation programs are most often reserved to COPD patients or those with lower performance status [9]. Few data is available regarding a full training program based on athletic intervention reserved to highly performant patients, in the absence of comorbidity. We thus aim at validating an athletic training program aiming at improving performance and quality of life.

### Impact of Lung Cancer Surgery

1.1

Anatomical lung resection remains the standard curative option for patients with early‐stage non‐small cell lung cancer (NSCLC). However, even in individuals with preserved baseline lung function and favorable performance status, surgery often leads to a measurable decline in pulmonary mechanics, cardiopulmonary fitness, muscle strength, and health‐related quality of life (HRQoL). This decline is multifactorial, stemming from pain, reduced ventilatory function, systemic inflammation, muscle catabolism, and prolonged inactivity during recovery [10, 11, 12]. Furthermore, impaired postoperative functional status has been associated with poorer long‐term outcomes, including increased morbidity, delayed return to normal activity, and reduced tolerance to potential adjuvant therapies [13]. Consequently, the postoperative period presents a critical window for targeted interventions aimed at restoring, and ideally enhancing, physical performance.

### Role of Respiratory Physiotherapy in Early Recovery

1.2

Respiratory physiotherapy has a well‐established role in the prevention of postoperative pulmonary complications, particularly atelectasis and pneumonia. Interventions such as inspiratory muscle training (IMT), positive expiratory pressure (PEP), active cycle of breathing techniques and thoracic expansion exercises have demonstrated benefits in preserving lung volume, improving mucus clearance, and re‐establishing diaphragmatic function [14, 15, 16]. These strategies have been associated with reduced post‐operative complications rates, shorter length of hospital stays, and faster weaning from oxygen therapy [17]. Importantly, early implementation of respiratory physiotherapy enhances patients' readiness to engage in more advanced physical activity, forming the foundation for progressive rehabilitation models.

### From Pulmonary Rehabilitation to Progressive Exercise Training

1.3

While standard pulmonary rehabilitation programs have historically focused on patients with COPD or limited functional reserve, there is a growing recognition of the need to extend exercise‐based interventions to high‐performance status postoperative cancer patients. The ATHENA study responds to this unmet need by proposing a mesocycle‐based, progressively loaded exercise program, designed to maximize adaptive physiological responses while maintaining safety. ATHENA model does not rely on acute spikes in workload. Instead, it incorporates: (i) structured progression over time, with gradual increases in session complexity and training volume; (ii) supervised aerobic, anaerobic and resistance training, tailored to patient capacity; (iii) integration of motor science principles, including recovery cycles, overload management, and biomechanical optimization, iv) continuous monitoring through VO₂ max, lung function test (FEV₁, DLCO), METs, and standardized HRQoL tools. This structured approach allows for physiological adaptation without exceeding individual safety thresholds an essential consideration in oncologic rehabilitation.

### Evidence Supporting Exercise‐Based Rehabilitation: Literature Review

1.4

In recent years, structured exercise interventions have been explored to mitigate these challenges and enhance postoperative outcomes.

#### Preoperative Exercise Training

1.4.1

Preoperative exercise programs have demonstrated significant benefits in reducing postoperative complications and enhancing recovery. A Cochrane systematic review encompassing 10 studies with 636 participants found that preoperative exercise training led to a 55% reduction in the risk of postoperative pulmonary complications compared to standard care. Additionally, these interventions were associated with shorter hospital stays and improved preoperative fitness levels. Further supporting these findings, a meta‐analysis by Cavalheri et al. reported that preoperative exercise training significantly decreased the length of hospital stay by approximately 5 days and reduced postoperative complications. Improvements in exercise capacity, as measured by the 6‐min walk distance (6MWD), were also observed [18, 19].

#### Postoperative Exercise Training

1.4.2

Postoperative exercise interventions have been shown to enhance functional recovery and quality of life in NSCLC patients. A systematic review and meta‐analysis of randomized controlled trials indicated that postoperative exercise training significantly improved physical and mental health domains of the SF‐36 quality of life questionnaire. However, the effects on exercise capacity and respiratory function were less conclusive, suggesting the need for longer or more intensive training programs. Another meta‐analysis focusing on postoperative recovery highlighted that exercise interventions led to significant improvements in forced expiratory volume in 1 s (FEV₁), quadriceps strength, and alleviation of dyspnea. These findings underscore the role of exercise in enhancing both pulmonary function and overall physical performance during recovery [20, 21, 22].

#### Combined Pre‐ and Postoperative Exercise Programs

1.4.3

Integrating exercise training both before and after surgery may offer synergistic benefits. A comprehensive review by Mainini et al. emphasized the importance of combining aerobic training with respiratory exercises, such as IMT and airway clearance techniques, to address the multifaceted needs of NSCLC patients. The authors advocate for multidisciplinary rehabilitation programs that are tailored to individual patient profiles, including considerations for comorbidities like chronic obstructive pulmonary disease (COPD) [18, 22].

#### Implications for Clinical Practice

1.4.4

The accumulating evidence supports the incorporation of structured exercise programs into the perioperative care of NSCLC patients. These interventions not only reduce the risk of postoperative complications but also enhance functional capacity and quality of life. Nevertheless, further high‐quality randomized controlled trials are needed to establish standardized protocols regarding the optimal timing, intensity, and components of exercise programs for this patient population.

## ATHENA Study Design

2

### Study Rationale and Aim

2.1

As reported above, there is a strong rationale for rehabilitation after surgery for lung cancer since it impacts on chronic symptoms and lung function. This approach is generally reserved to COPD patients or those with lower performance status [19]. Few data is available regarding a full training program based on athletic intervention reserved to highly performant patients, in absence of comorbidity. We thus aim at validating an athletic training program aiming at improving performances and quality of life. Patients will be selected based on their performance status and on multidisciplinary evaluation by the local Interdisciplinary Thoracic Tumor Board.

### Study Design

2.2

This is a single‐center, single‐arm pilot interventional study. The primary purpose of this pilot study is to evaluate the feasibility, safety, and preliminary functional effects of a structured athletic training program administered after curative‐intent lung resection for NSCLC in a highly selected population with preserved performance status. Ten patients will be enrolled and followed for 6 months during the intervention period, with repeated assessments performed at baseline, 3 months, and 6 months (Figure 1).

**Figure 1 hsr272512-fig-0001:**
[figure not shown]
ATHENA study timeline.

### Study Objectives

2.3

The primary exploratory objective of the study is to assess the change in peak oxygen uptake (VO₂peak, mL·kg⁻¹·min⁻¹), measured by cardiopulmonary exercise testing (CPET), from baseline to 6 months in patients undergoing curative‐intent surgery for early‐stage NSCLC and enrolled in the ATHENA training program. VO₂peak/VO₂max reflects the highest oxygen uptake achieved during incremental exercise testing and should not be confused with resting oxygen consumption, whereas 1 MET corresponds to 3.5 mL O₂·kg⁻¹·min⁻¹ at rest. Secondary study objectives are improvement of: (i) the change of pulmonary function (FEV1 and DLCO and VO_2_ max) measured at baseline, at the 3rd and at the 6th month of the study. The latter is defined as the amount of oxygen consumed while sitting at rest and is equal to 3.5 ml O_2_ per kg body weight x min; (ii) The quality of life will be assessed by the EORTC QLQ‐C30 (vers. 3) Questionnaire a 30‐item instrument designed to measure quality of life in all cancer patients [23]; (iii) improvement in caloric consumption measured by metabolic equivalents. Although being a pilot study, demographic exploratory outcomes would be assessed. Results will be analyzed to evaluate if observed differences in outcomes could be related to gender and/or age of the subjects since it is conceivable that the two variables could affect athletic performances and primary and secondary outcomes.

### Patients' Identification and Selection

2.4

Being a pilot study, the study population would be defined by subjects who underwent radical pulmonary surgery for stage IA lung cancer and whose performance status is judged as high after multidisciplinary evaluation by the Interdisciplinary Tumor which is active in our Institution. The population to be studied will be out‐patients subjects followed at the Pneumology Unit after thoracic surgery for lung cancer. To mitigate the study risks, the identification and selection of patients will be defined during the lung cancer board meeting when all lung cancer cases diagnosed and treated at Fondazione IRCCS Policlinico San Matteo and associated spoke centers are discussed: (i) study participants will be recruited at Fondazione IRCCS Policlinico San Matteo, Pneumology Unit among those patients affected by lung cancer and addressed to surgery with a curative setting. After surgery each case will be rediscussed multidisciplinary and patients with higher performance status, defined by ECOG score 0 and CCI score from 1 to 4, will be selected for the study (website https://www.mdcalc.com/calc/3170/eastern-cooperative-oncology-group-ecog-performance-status; https://www.mdcalc.com/calc/3917/charlson-comorbidity-index-cci); (ii) specifically the ECOG Performance Status Scale describes a patient's level of functioning in terms of their ability to care for themselves, daily activity, anphysical ability. An ECOG score of 0 identifies a fully active person, able to perform all pre‐disease services without limitations. The Charlson Comorbidity Index (CCI) is used to classify comorbid conditions which may influence mortality risk. The severity of comorbidity from mild (CCI scores of 1–2) to moderate (CCI scores of 3–4) is used for the selection of patients in the study. Higher scores indicate a more severe condition and, consequently, a worse prognosis. If the patient agrees to participate, the informed consent form will be signed and dated. Written informed consent must be documented before any study‐specific screening procedure. The overall eligibility of the subject to participate in the study will be assessed once all screening values are available (a schematic overview of the clinical timeline and enrollment strategy is provided in Figure 2). Patients meeting all inclusion and none of the exclusion criteria will be enrolled. No payment or compensation will be given to study participants.

**Figure 2 hsr272512-fig-0002:**
[figure not shown]
Athena details. Criteria for clinical trial enrollment, training program and ethical approval [24].

#### Inclusion Criteria

2.4.1

Patients will be considered eligible if they meet all of the following criteria:
–Age ≥ 18 years;
–Histologically confirmed NSCLC treated with curative‐intent lung resection;–Pathological stage IA disease;–ECOG Performance Status 0;–Charlson Comorbidity Index between 1 and 4;–Clinical stability at approximately 30 days after surgery;–Ability to undergo CPET and supervised exercise training;–Ability to understand study procedures and provide written informed consent;–Absence of contraindications to exercise training according to sports medicine evaluation.

#### Exclusion Criteria

2.4.2

Patients will be excluded in the presence of any of the following:
–ECOG Performance Status ≥ 1;–Severe cardiovascular, respiratory, neurological, musculoskeletal, or psychiatric comorbidities limiting safe exercise participation;–Postoperative complications preventing participation in the training program; ‐Need for adjuvant systemic treatment during the intervention period, if considered incompatible with the exercise protocol;–Documented disease recurrence before enrollment;–Inability to adhere to scheduled visits or supervised training sessions;–Any clinical condition judged by the investigators or sports medicine team to make participation unsafe.

#### Withdrawal Criteria

2.4.3

Participants may be withdrawn from the study for any of the following reasons:
–Withdrawal of informed consent;
–Occurrence of a serious adverse event or any clinical condition making continued participation unsafe;–Disease recurrence or initiation of anticancer treatment judged incompatible with protocol continuation;–Investigator decision based on safety concerns.

All reasons for withdrawal will be recorded.

### Statistical Analysis

2.5

Categorical variables will be summarized as counts and percentages, whereas continuous variables will be described using mean and standard deviation or median and interquartile range, as appropriate according to their distribution. All statistical analyses will be performed using Stata 18 (StataCorp. 2023. *Stata Statistical Software: Release 18*. College Station, TX: StataCorp LLC.). Given the longitudinal design of the study, outcomes collected at baseline, 3 months, and 6 months will be analyzed using repeated‐measures approaches. Continuous outcomes, including VO₂ peak, pulmonary function parameters, and quality‐of‐life scores, will be primarily analyzed using linear mixed‐effects models, including time as a fixed effect and patient as a random effect, in order to account for within‐subject correlation across repeated measurements. For exploratory analyses, age and sex will be included as covariates in the fixed part of the models. If model assumptions are not met, appropriate generalized linear mixed models or generalized estimating equations will be considered.

Results will be reported as estimated changes over time with 95% confidence intervals. Given the pilot nature of the study and the limited sample size, all efficacy analyses will be considered exploratory and interpreted with caution. A two‐sided alpha level of 0.10 will be used for inferential analyses. Adverse events will be summarized descriptively, and their incidence will be reported with 95% confidence intervals. As a sensitivity analysis, a completer‐only analysis will also be performed.

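### Read plainly, age and sex enter the mixed models as main effects, which cannot show whether change from baseline differs by age or sex

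*Protocol article*

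**What the plan says.** Section 2.3 (Study Objectives) sets a demographic exploratory aim: "Results will be analyzed to evaluate if observed differences in outcomes could be related to gender and/or age of the subjects". Its reason is that "the two variables could affect athletic performances and primary and secondary outcomes".

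Those outcomes are largely changes. The Discussion paragraph of the abstract says "The primary exploratory endpoint will be the change in CPET‐derived VO₂peak from baseline to 6 months", and Section 2.3 defines the primary objective in the same way. The abstract adds that "secondary endpoints will include changes in FEV₁, DLCO, MIP/MEP, METs, muscle power, and EORTC QLQ‐C30 scores".

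Section 2.5 (Statistical Analysis) specifies linear mixed models "including time as a fixed effect and patient as a random effect". For age and sex it provides: "For exploratory analyses, age and sex will be included as covariates in the fixed part of the models". On reporting it says: "Results will be reported as estimated changes over time with 95% confidence intervals". The article names no time-by-age or time-by-sex term and no change by subgroup.

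On size, Section 2.2 says: "Ten patients will be enrolled and followed for 6 months during the intervention period". Visits are at baseline, 3 months and 6 months.

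**The concern.** The aim and the model do not meet. If the outcome is a change, asking whether sex or age affects it means asking whether the change differs between men and women, or along the age range. A model with time, age and sex as separate additive terms gives every patient the same expected change. The difference of interest is then set to zero by the model and not estimated.

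Two things are at stake, both modest. A difference in training response by sex or age would have no term in which to appear. And a sex or age coefficient, which reflects only level (for example, a higher VO₂peak in one sex at every visit), could be taken for a differential effect of the programme. The article says the pilot is meant to inform larger studies, where such a misreading could carry over.

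**Working it through.** The article gives no figure on this point to reproduce: no SD, effect size or precision statement. The check is algebraic, followed by a precision calculation under stated assumptions.

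**1. What main effects can show.** With fixed time, random patient, and age and sex as covariates (Section 2.5):

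E[Y_it] = b0 + b_t + g·age_i + d·sex_i, with b_0 = 0 at baseline.

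The expected 6-month change for patient i is

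E[Y_i6 − Y_i0] = (b0 + b_6 + g·age_i + d·sex_i) − (b0 + g·age_i + d·sex_i) = b_6.

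Sex and baseline age do not vary within a patient, so g and d cancel. The change is b_6 for everyone, while g and d measure average level over the visits.

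**2. Effect on the time contrasts.** With complete data, the time contrasts in a random-intercept model rest on within-patient differences alone. Covariates that are constant within a patient do not alter them or their standard errors, unless the between-patient variance is estimated as zero.

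**3. Illustration only.** One data set was simulated with assumed values: 10 patients, 5 per sex, three visits, and a true sex difference in 6-month change of 4 units.

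| Model | 6-month result |
|---|---|
| Time only | time effect 1.4056 (SE 0.8555) |
| Time + age + sex | time effect 1.4056 (SE 0.8555); predicted change 1.41 in both sexes |
| Time × sex and time × age | sex difference in change 3.72 (SE 1.52) |

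The observed mean changes in that data set were −0.46 and 3.27. The figures show the cancellation; they do not predict this trial.

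**4. Precision of the sex difference in change.** The article gives neither the SD of change nor the sex split, so results are in SD units over assumed splits. For n1 and n2 complete patients (n1 + n2 = 10, 8 degrees of freedom, t = 2.306), comparing change scores:

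95% half-width = 2.306 × √(1/n1 + 1/n2) × SD

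- 5:5: 2.306 × √0.400 = 1.46 SD
- 7:3: 2.306 × √0.476 = 1.59 SD
- 8:2: 2.306 × √0.625 = 1.82 SD

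If the SD of change in VO₂peak is assumed to be 2 mL/kg/min, these are about 2.9, 3.2 and 3.6 mL/kg/min. They scale in proportion to the SD: at 5:5, about 1.5 for an SD of 1 and 4.4 for an SD of 3. A mixed model that pools residual variance over visits has more degrees of freedom and may give a somewhat narrower interval.

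**5. What a test could detect.** At the protocol's two-sided alpha of 0.10 and an assumed 80% power, the smallest detectable sex difference in change is about 1.73 SD (5:5), 1.89 SD (7:3) or 2.16 SD (8:2), from the noncentral t distribution. For age, with t = 1.860 on 8 degrees of freedom, the correlation with change must exceed 1.860/√(8 + 1.860²) = 0.55 in absolute value to reach p < 0.10.

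**The case against.** **The text does not exclude interactions.** Section 2.5 does not say that age and sex enter as main effects only, and interaction terms also belong to the fixed part of a model. A fuller protocol or analysis plan, not shown, may name them. So a reader might infer that the protocol rules interactions out; it does not. What stands is that Section 2.5 does state how age and sex will enter, and the plain reading of that sentence is main effects. The point concerns a stated analysis that does not match its aim, not omitted detail.

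**The aim could partly concern levels.** Section 2.3 does not speak of differences in change over time, and athletic performance can naturally be read as a level. Main effects do address levels. This stands in part, and it is why rewording the aim is an equally valid remedy. It does not remove the mismatch, because the same sentence extends to the primary and secondary outcomes, which are largely defined as changes.

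**Ten patients cannot support interactions.** They cannot support a useful test, as step 5 shows. A reader might infer that adding the terms would reliably reveal a difference in response; at this size it would not. But imprecision is a reason to report an interval and say how wide it will be, not a reason to estimate a different quantity.

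**The harm is conjectural.** Nothing in the article says that a sex coefficient will be presented as a programme effect. This is fair: misreading is a risk, not a stated intention.

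**Conclusion.** The point holds in a limited form. On the plain reading of Section 2.5, the age and sex terms cannot show whether change from baseline differs by age or sex, although Section 2.3 asks whether outcomes largely defined as changes are related to them. The cancellation is exact algebra. The invariance of the time contrasts and their standard errors assumes complete data.

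Severity is minor to moderate. The aim is a secondary exploratory one in a ten-patient pilot, and Section 2.5 already treats all efficacy analyses as exploratory. A reader might infer that the primary result is compromised; it is not, since the estimated 6-month change is the same with or without these covariates when data are complete.

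The precision figures rest on ten complete patients and assumed sex splits. The mL/kg/min values also rest on an assumed SD of change.

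**What to change.** In Section 2.5, replace the sentence on age and sex with wording such as:

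*Separate exploratory models, one modifier at a time, will add a time-by-sex or a time-by-age (continuous) interaction. The difference in 6-month change between the sexes, and per 10 years of age, will be reported with confidence intervals and without claims of significance.*

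Add one sentence on expected imprecision in SD units: with ten complete patients, the 95% half-width for the sex difference in change is about 1.46 SD of change at 5:5, 1.59 at 7:3 and 1.82 at 8:2.

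If only differences in level are intended, leave the model as it is and reword the aim in Section 2.3 to say so.

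Either route costs a sentence or two and needs no new data or visits. The one consequence of the first is that the wide intervals become visible.

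### Estimated changes are tested at a two-sided alpha of 0.10 but reported with 95% confidence intervals, and the plan does not reconcile the two levels

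*Protocol article*

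**What the plan says.** All the relevant text is in the second paragraph of section 2.5 (Statistical Analysis) of the protocol article.

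- On estimation: "Results will be reported as estimated changes over time with 95% confidence intervals".
- On testing: a two-sided "alpha level of 0.10 will be used for inferential analyses".
- On the status of the results: "all efficacy analyses will be considered exploratory and interpreted with caution".
- On safety: "Adverse events will be summarized descriptively, and their incidence will be reported with 95% confidence intervals".

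The changes come from linear mixed-effects models "including time as a fixed effect and patient as a random effect", fitted to VO₂peak, pulmonary function and quality-of-life scores at baseline, 3 months and 6 months. Section 2.3 (Study Objectives) names the lead outcome: "The primary exploratory objective of the study is to assess the change in peak oxygen uptake", from baseline to 6 months. Section 2.2 (Study Design) gives the size: "Ten patients will be enrolled and followed for 6 months during the intervention period".

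The document gives no 90% interval, no reason for the two levels and no statement of how to read a result on which they differ. It states no target effect, SD, power or degrees-of-freedom method.

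**The concern.** A two-sided test at level alpha and a two-sided interval at confidence 1 − alpha, taken from the same estimate and standard error, carry the same information: the test rejects exactly when the interval excludes zero. The plan breaks that link by testing at 0.10 and drawing the interval at 95%. Both apply to the same model-estimated changes, including the primary one in VO₂peak.

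A reader of the results could then meet an improvement described as statistically significant beside an interval that covers zero. The authors would have to decide, with the data in view, which of the two to stress. This is not a detail left for a fuller document to supply. The article fixes both numbers, and they do not match.

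**Working it through.** **Inputs.** Two-sided alpha 0.10 and confidence level 95% (section 2.5); 10 patients (section 2.2); 3 assessment times (sections 2.2 and 2.5). The degrees of freedom and the true standardised changes below are assumptions, because the document gives neither.

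**Step 1: do the two levels agree?** The alpha implied by a 95% interval is 1 − 0.95 = 0.05, not 0.10. The interval that matches alpha 0.10 has confidence 1 − 0.10 = 90%. The stated pair does not agree.

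**Step 2: where do test and interval part company?** The test at 0.10 rejects when |estimate/SE| exceeds the 0.95 quantile of the reference distribution. The 95% interval excludes zero only above the 0.975 quantile.

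| Reference distribution | Significant at 0.10 above | 95% interval excludes zero above |
|---|---|---|
| Normal | 1.645 | 1.960 |
| t, 18 df: (10 − 1) × (3 − 1), complete data | 1.734 | 2.101 |
| t, 9 df: paired change, 10 − 1 | 1.833 | 2.262 |

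Between the two limits 0.05 < p < 0.10, and the messages differ. The zone exists whichever reference is used.

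**Step 3: size on the outcome scale.** For a paired change, t = mean change / (SD of the change / √10). With 9 df the zone runs from 1.833/√10 = 0.58 to 2.262/√10 = 0.72 SD of the change.

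**Step 4: an example.** Take estimate/SE = 2.0 with 9 df, in units of the SE.

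- p = 0.077, so significant at 0.10.
- 95% interval: 2.0 ± 2.262 = (−0.26, 4.26), which includes zero.
- 90% interval: 2.0 ± 1.833 = (0.17, 3.83), which excludes zero.

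**Step 5: how often?** The probability of landing in the zone is P(|T| > 1.833) − P(|T| > 2.262). Here T is noncentral t with 9 df and noncentrality d√10, and d is the true mean change divided by the SD of the change.

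| Assumed d | P(reject at 0.10) | P(reject at 0.05) | Difference |
|---|---|---|---|
| 0 | 0.1000 | 0.0500 | 0.0500 |
| 0.3 | 0.2274 | 0.1361 | 0.0913 |
| 0.5 | 0.4282 | 0.2932 | 0.1350 |
| 0.7 | 0.6549 | 0.5064 | 0.1485 |
| 0.8 | 0.7545 | 0.6162 | 0.1382 |
| 1.0 | 0.8975 | 0.8031 | 0.0944 |

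For d above zero, the last column is also the power given up by moving the test from 0.10 to 0.05.

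**The case against.** The strongest reply is that the plan names only one testing level, 0.10, and gives the 95% interval for reporting precision. Nowhere is exclusion of zero made a criterion. A reader might infer that the plan contains two conflicting decision rules, but the text does not say so: there is one rule and an interval that is not aligned with it. A report that shows the estimate, the 95% interval and the p-value together would not mislead anyone about precision. The study is also a ten-patient, single-arm pilot with no success criterion, no go/no-go rule and no sample-size claim that rests on the test. All of this stands, and it limits the severity. It does not remove the mismatch, since the plan still attaches a significance level to estimates whose stated interval answers to another level.

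A reader might also go further and infer that a 10% level across all secondary outcomes makes false improvements close to certain. With 20 independent tests, for example, 1 − 0.9^20 = 0.88. The documents do not support that figure.

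- The abstract lists seven secondary measures (FEV₁, DLCO, MIP, MEP, METs, muscle power and QLQ-C30). A count of 20 needs some of them to be split and nearly all to be tested at both follow-up times.
- Section 2.6 places the muscle-power evaluation before and after training, so a 3-month test of it is not established.
- Measurements on the same ten patients are not independent.
- The test is two-sided, so under no change half of the false positives would be apparent declines.

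With efficacy already labelled exploratory, restricting tests to a single contrast would be a preference and not the correction of an error.

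**Conclusion.** The point holds as a mismatch between two stated figures: alpha 0.10 goes with a 90% interval, and the plan specifies 95% for the same changes without explanation. Results with 0.05 < p < 0.10 would be called significant with an interval that includes zero. On the paired-change illustration the chance of this is 5% with no true change and about 9 to 15% for standardised changes of 0.3 to 1.0.

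Those probabilities rest on 10 complete patients, 9 df and assumed effect sizes. The planned mixed model may use other degrees of freedom, but the normal and 18-df limits lead to the same conclusion. Severity is minor to moderate. Neither a 95% interval nor a 10% test is wrong in itself in a pilot; the defect is the unreconciled pairing. The 95% intervals for adverse-event incidence are descriptive, have no test attached and are not affected.

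**What to change.** Before any outcome data are seen, change section 2.5 in one of two ways.

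- **Preferred:** keep the two-sided alpha of 0.10 and report 90% confidence intervals for the tested changes, with VO₂peak from baseline to 6 months named as the lead contrast. The 95% intervals may be shown in addition if they are labelled descriptive. The cost is about one sentence, with no change to the sample size, the model or the data collected.
- **Alternative:** keep the 95% intervals and set alpha to 0.05. This also removes the discordant zone, but it is not free. The article claims no power, so no stated figure would need revising; real power nevertheless falls by about 9 to 15 percentage points for standardised changes of 0.3 to 1.0, for example from 43% to 29% at 0.5.

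Leave the 95% intervals for adverse-event incidence as they are.
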